#### Exclusion criteria

2.3.2

Presence of serious diseases affecting the heart, liver, kidneys, or other major organs.Patients scheduled to undergo surgery, radiotherapy, or chemotherapy during the trial period.Pregnant or lactating women.Presence of intestinal perforation, hemorrhage, obstruction, or any other contraindications to moxibustion.Individuals with psychiatric conditions or substance abuse (drugs, alcohol, medications) compromising communication.Patients with ulcers, sores, or localized skin infections at the proposed moxibustion sites.Patients with respiratory diseases, a known allergy to moxibustion, or any other conditions for which moxibustion therapy is contraindicated.

### Randomization

2.4

The SAS 9.4 (SAS Institute Inc., Cary, NC) software’s “Proc Plan” process will generate random numbers that will be used to divide the patients into two groups. After being sealed in envelopes, the random allocation cards will be opened one after the other according to the patients’ visits. Based on the cards in the envelopes, the researcher will divide the eligible individuals in a 1:1 ratio between the moxibustion group and the placebo moxibustion group. Each participant will be made conscious that they have an equal probability of being placed in either group.

### Blinding

2.5

In the course of the study, all participants, including subjects, efficacy evaluators, data analysts, and statistical analysts, with the exception of the acupuncturists, will be blinded to the group assignments. To preserve this blinding, rigorous measures will be enacted to limit the exchange of relevant information among participants. These measures include the use of separate treatment rooms and the requirement for participants to wear eye masks. At the end of the 4-week treatment period, blinding assessment will be conducted using a questionnaire. Patients will be asked to respond to the question: “Which treatment do you believe you received?” with options including “Moxibustion, Placebo moxibustion, or Uncertain.” The evaluation will be performed using Bang’s Blinding Index(BI) system for quality control of blinding, with the BI for each group calculated through a mathematical model. BI will be used to evaluate blinding quality. Values close to 0 indicate successful blinding, while values further from 0 suggest potential unblinding. The BI results for each group will be interpreted descriptively to assess the adequacy of blinding.

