### Sample size calculation

2.9

Based on the preliminary research results, it was observed that 40% of patients in the moxibustion group and 10% in the placebo group exhibited a decrease of at least 3 points on the BFI at week 4. Calculations indicate that the sample size of 58 patients would ensure a study power of at least 80%, with a two-sided significance level of 0.05. To adjust for an anticipated dropout rate of 20%, 37 patients will be finally taken from for each group.

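### A Bang's index close to 0 is read as successful blinding with no measure of precision, although at 29 to 37 answers per arm it does not exclude appreciable unblinding (minor)

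*Protocol article*

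**What the plan says.** Section 2.5 (Blinding) of the protocol article plans a single blinding check: "At the end of the 4-week treatment period, blinding assessment will be conducted using a questionnaire". Patients choose between moxibustion, placebo moxibustion and uncertain. Bang's index is then obtained separately in each arm, "with the BI for each group calculated through a mathematical model".

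The section goes on to say how the result will be read: "Values close to 0 indicate successful blinding, while values further from 0 suggest potential unblinding". It adds: "The BI results for each group will be interpreted descriptively to assess the adequacy of blinding". No cut-off, confidence interval, test or expected share of 'Uncertain' answers is given.

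The number of possible answers follows from section 2.9 (Sample size calculation): "To adjust for an anticipated dropout rate of 20%, 37 patients will be finally taken from for each group".

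**The concern.** The reading in section 2.5 goes from the value of the index to a conclusion about blinding. In arms of this size the index is imprecise. A value near 0 may come from a blinded arm, or from an arm in which clearly more patients guess right than wrong. Calling it successful blinding claims more than the data can carry. Conversely, a moderate departure from 0 may be chance.

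This matters here for three reasons:

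- The primary outcome is a response on a patient-rated fatigue scale (section 2.7.2).
- The arms differ in skin temperature, 43 ± 1 °C against 37 ± 1 °C (sections 2.6.1 and 2.6.2), and patients may feel that difference.
- The Discussion acknowledges that moxibustion is hard to blind and rests the rigour of the comparison on the placebo device.

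Readers will use the blinding statement to judge how far to trust the efficacy result.

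**Working it through.** **Inputs from the protocol article**

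- 37 patients per arm and 20% anticipated dropout (section 2.9).
- Three answer options, asked once at the end of week 4, with the index calculated per arm (section 2.5).

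**Input assumed.** The share *u* answering 'Uncertain' is not in the document, so it is varied from 0% to 50%.

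**Step 1: reproduce the plan's own figures.** With response rates of 40% and 10%, two-sided 5% significance and 80% power, the unpooled normal approximation gives (1.960 + 0.842)² × (0.4 × 0.6 + 0.1 × 0.9) / 0.3² = 28.8. That rounds up to 29 per arm, or 58 in total, as stated. Dividing by 0.8 gives 29 / 0.8 = 36.25, so 37 per arm, as stated. If 20% of 37 do not reach week 4, 37 × 0.8 = 29.6, so about 29 to 30 answers per arm. The document gives no figure for the precision of the index.

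**Step 2: precision of the index.** With three options the index is BI = p_c − p_i, the proportion guessing correctly minus the proportion guessing incorrectly. Its standard error is

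SE = √{[p_c + p_i − (p_c − p_i)²] / n}.

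At BI = 0 this becomes √[(1 − u)/n], and the 95% half-width is 1.96 × SE.

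| Share 'Uncertain' | n = 37 | n = 29 |
|---|---|---|
| 0% | ±0.322 | ±0.364 |
| 20% | ±0.288 | ±0.326 |
| 30% | ±0.270 | ±0.305 |
| 50% | ±0.228 | ±0.257 |

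As an example, suppose 13 patients guess right, 13 guess wrong and 11 are uncertain, out of 37. The index is 0, SE = √[(26/37)/37] = 0.138, and the 95% interval is −0.27 to 0.27. For scale, at 30% 'Uncertain' a true index of 0.3 means 50% right and 20% wrong.

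**Step 3: how often chance moves a blinded arm away from 0.** These are exact trinomial probabilities for one arm with a true index of 0.

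| Share 'Uncertain' | \|BI\| ≥ 0.2, n = 37 | \|BI\| ≥ 0.2, n = 29 | \|BI\| ≥ 0.3, n = 37 | \|BI\| ≥ 0.3, n = 29 |
|---|---|---|---|---|
| 0% | 18.8% | 26.5% | 4.7% | 13.6% |
| 30% | 14.1% | 22.3% | 2.3% | 5.8% |
| 50% | 8.1% | 14.8% | 0.7% | 2.5% |

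**Step 4: how often a partly unblinded arm looks close to 0.** With a true index of 0.3, the observed index lies within ±0.2 in about 18% to 29% of arms, at both n = 37 and n = 29, over the same range of *u*. The thresholds 0.2 and 0.3 are illustrations; the protocol article sets neither.

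**The case against.** The strongest reply is that there is no decision rule to criticise. Section 2.5 explains in general terms what the index means and then says it is read descriptively. No cut-off or pass/fail call is stated, and neither the sample size nor any analysis in section 2.10 depends on it. The article also condenses a fuller protocol, and a confidence interval for a quality-control index is a detail that may sit there or in the statistical analysis plan. Most of this stands. It makes the point minor, and the absence of an interval from the article is not in itself the fault. What remains is the sentence that equates a value near 0 with success: an interval given elsewhere would not make that sentence right.

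A reader might be tempted by three stronger readings. The document does not support them.

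- *That the trial will formally certify blinding from a bare point estimate.* The text neither says the interval will be omitted nor attaches a consequence to the index.
- *That the margin of error is one known figure, such as ±0.27.* That value needs all 37 patients to answer and about 30% to choose 'Uncertain'. With other shares, or with the stated dropout, it differs, so only a range can be given.
- *That values away from 0 often arise by chance.* This depends on how far away. It is fair for departures of around 0.2. Departures of 0.3 or more are uncommon: about 1% to 5% of blinded arms at 37 answers and 3% to 14% at 29.

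**Conclusion.** The point holds in a limited form. With 29 to 37 answers per arm and 0% to 50% answering 'Uncertain', an observed index of 0 is compatible with true values up to somewhere between 0.23 and 0.36. It can support a statement that unblinding was not clearly seen, but not that blinding succeeded. This limb needs no cut-off and holds across the whole assumed range. The second limb, that moderate departures can be chance, is conditional on the illustrative 0.2 threshold.

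Severity is minor. The index is descriptive, and the primary analysis, sample size and treatment are untouched. What changes is the claim about blinding that the trial may make.

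**What to change.** In section 2.5:

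1. State that Bang's index will be reported in each arm with its 95% confidence interval.
2. Replace the reading of values close to 0 as successful blinding. When the interval includes 0, report no clear evidence of unblinding together with the range of index values not excluded. Take that range from the observed data rather than fixing a number in advance.
3. Suggest unblinding only when the interval excludes 0, and report the sign, since a negative index means more wrong than right guesses.

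A fixed success margin such as 0.2 is not needed. Every half-width in the step 2 table exceeds 0.2, so even an observed index of exactly 0 would fail to meet it. A one-sided version would also label a strongly negative index as success.

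The cost is one sentence and one standard formula applied to answers already planned for collection. The downside is a less favourable blinding statement.

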### Interventions

2.6

#### Moxibustion group

2.6.1

Patients allocated to the intervention group will receive moxibustion therapy targeting the midline acupoints Guan Yuan (CV4) and Qi Hai (CV6), together with bilateral Zu San Li (ST36) acupoints in a supine position. The acupoint locations are determined based on the The People’s Republic of China’s State Standard (GB/T 12346-2021). Detailed illustrations of the acupoint locations are provided in **Figure 2** and **Table 2**. In the moxibustion group, patients will be treated with pure moxa sticks (diameter: 2.8 cm; Hanyi, Nanyang, China) ignited and placed on a stand to maintain 3–5 cm from the acupoints. The skin temperature at the acupoints will be regulated at 43 ± 1 °C and monitored using an infrared thermometer (Fluke 62, Fluke Corporation, Everett, WA, USA) (13). The moxibustion device used in the study is shown in **Figure 3**.Two 30-minute sessions of treatment will be offered twice a week for a total of eight sessions spread over four weeks. During treatment, the burning moxa stick will be monitored continuously to maintain a stable thermal stimulus. Ash will be removed promptly as needed to ensure consistent combustion and to avoid excessive heat fluctuation or ash dropping during the procedure.

**Figure 2 f2:**
[figure not shown]
Location of acupoints in the moxibustion group and placebo moxibustion group. CV 4: Guan Yuan; CV6: Qi Hai; ST 36:Zu San Li.

**Table 2 T2:** The location of acupoints in the moxibustion group and placebo moxibustion group.

Acupoint	Location
Zu San Li(ST36)	On the outer side of the lower leg, 3 *cun* below the outer knee, and one horizontal finger’s breadth away from the anterior edge of the tibia.
Guan Yuan(CV4)	On the lower abdomen midline, 3 *cun* below the umbilicus.
Qi Hai(CV6)	On the lower abdomen midline, 1.5 *cun* below the umbilicus.

*cun*: a proportional body measurement used in acupuncture; one horizontal finger’s breadth: the width of the patient’s thumb at the interphalangeal joint, or a proportional digital measurement depending on your standard source.

**Figure 3 f3:**
[figure not shown]
Moxibustion and placebo moxibustion device. **(A)** Moxibustion device; **(B)** Placebo moxibustion device.

#### Placebo moxibustion group

2.6.2

Patients allocated to the placebo moxibustion group will undergo treatment at identical acupoints as those in the moxibustion group, using the same type of moxa sticks. However, the placebo moxibustion will be applied at a distance of 8–10 cm from the acupoints to maintain a temperature of 37 ± 1 °C. The device utilized for the placebo moxibustion is depicted in **Figure 3**. Additionally, the duration and number of sessions for the placebo moxibustion treatment will mirror those of the moxibustion group.

#### Management of concomitant anticancer treatments

2.6.3

To minimize potential confounding effects on fatigue severity and immune-related outcomes, patients who are scheduled to undergo surgery, radiotherapy, or chemotherapy during the intervention period will not be enrolled in this trial. At baseline, detailed information on prior and current anticancer treatments will be collected, including surgery, chemotherapy, radiotherapy, targeted therapy, immunotherapy, and supportive care, as well as the interval since the last anticancer treatment. During the study period, any clinically relevant treatment changes or medical events that may affect fatigue or immune status, such as the initiation of new anticancer therapy, treatment escalation, infection, blood transfusion, or the use of hematopoietic growth factors or corticosteroids, will be documented in detail. These factors will be considered during data interpretation, and sensitivity or adjusted analyses will be performed if necessary to evaluate the robustness of the primary outcome.

### Outcomes

2.7

#### Medical history collections

2.7.1

The collected patient medical history will be data on participant demographics and medical history, including gender, age, height, weight, disease duration, tumor type, tumor stage, and treatment modalities.

#### Primary outcome

2.7.2

The primary outcome measure is the proportion of patients achieving a reduction of at least 3 points on the BFI at week 4. A responder-based endpoint was selected because it provides a clinically interpretable estimate of the proportion of patients achieving meaningful fatigue improvement. This approach is also consistent with prior symptom-management trial in CRF, in which the BFI has been used not only as a continuous measure of fatigue severity but also to classify clinically relevant improvement or normalization of fatigue status (14). In the present trial, a 3-point reduction was prespecified as an interpretable response threshold based on prior fatigue literature, the 0–10 scaling properties of the BFI, and the preliminary data used for sample size estimation, while continuous changes in BFI scores are also analyzed as secondary outcomes (15). BFI is a subjective and reliable measure assessing the level of fatigue in the past 24h and the impact of fatigue on patients. The questionnaire consists of nine items rated on a 0–10 scale, with a final score range of 0-10. Fatigue is rated as mild (1-3), moderate (4-6), or severe (7-10) (16).

#### Secondary outcomes

2.7.3

##### The changes in BFI scores

2.7.3.1

It will be evaluated at weeks 1,2,3,4, 8.

##### QLQ-C30

2.7.3.2

The quality of life (QoL) of cancer survivors is assessed using a detailed 30-item questionnaire. This instrument incorporates a global QoL scale alongside multiple functional scales that evaluate physical, role, cognitive, emotional, and social functioning. Furthermore, it features symptom scales that focus on pain, fatigue, and nausea and vomiting. The questionnaire also includes specific items that measure dyspnea, constipation, insomnia, appetite loss, diarrhea, and the financial repercussions of the illness (17). It will be assessed at weeks 0 and 4.

##### GAD-7

2.7.3.3

The brief anxiety self-assessment tool comprises 7 items, each evaluated on a scale ranging from 0 to 3, resulting in a cumulative score that can vary from 0 to 21. Scores 5–9 suggest the presence of mild anxiety, scores 10–14 indicate moderate anxiety, and scores 15–21 are indicative of severe anxiety (18). It will be assessed at weeks 0 and 4.

#### Biological specimen exploratory outcomes

2.7.4

Given that CRF has been associated with inflammation and immune dysregulation, exploratory biological outcomes were included to investigate whether symptom changes may be accompanied by changes in host immune status. Peripheral blood cell counts and serum T lymphocyte subsets were selected as clinically accessible exploratory indicators. Exploratory analysis of biological indicators include the following items: (1)Blood cell counts, which include leukocytes, hemoglobin, platelets, and lymphocytes. It will be evaluated at weeks 0 and 4. (2)Serum T lymphocyte subsets, which include CD3+, CD4+, CD8+, CD4+/CD8+. It will be evaluated at weeks 0 and 4.

#### Safety evaluation

2.7.5

Adverse events (AEs) linked with moxibustion are burns, allergic reactions, and blistering, along with potential worsening of pre-existing conditions due to the therapy. In the event of any AEs, it is imperative for the practitioner to promptly assess their severity and implement suitable interventions, such as removing the heat source or consulting a dermatologist for severe burns. Any AEs noticed during the study need to be documented in the “Adverse Event Form”. It is imperative that both the management protocols and the resultant outcomes of these AEs are dutifully recorded with precision. In the event that a participant experiences serious AEs during treatment, the clinical trial shall be assessed and potentially terminated at the discretion of the researchers. Treatment termination details, including final time and outcome, will be documented for statistical analysis of AEs.

### Data collection and management

2.8

Before initiating a clinical trial, researchers will engage in comprehensive training sessions that focus on the study protocol. To improve participant compliance, researchers must rigorously implement the process of informed consent, ensuring that participants possess a comprehensive understanding of the experimental requirements and agree to cooperate. The study will provide complimentary moxibustion treatment, conduct monitoring and evaluation of relevant indicators, offer transportation subsidies, and deliver healthcare guidance. Researchers meticulously adhere to clinical trial protocols and implement standard operating procedures to maintain rigorous quality control and ensure the effective execution of quality assurance systems in clinical trials.

The project team has established a data quality control group tasked with conducting both scheduled and unscheduled monitoring visits, as well as verifying the study’s data integrity. Clinical data for each participant will be gathered using CRFs. Following the completion of each participant’s observation session, the researcher is required to submit CRFs and informed consent documentation to the data quality control team for evaluation within three working days. During the supervision process, should any protocol deviations be identified, team members are required to complete a violation record. This record must include detailed documentation of the time of discovery, the timing and sequence of the incident, the underlying reasons, and the corresponding corrective actions. The record must be signed by the researcher and reported to the Ethics Committee in accordance with relevant regulations. In statistical and summary reports, the influence of protocol violations on the final data and conclusions is systematically analyzed, evaluated, and documented.

### Sample size calculation

2.9

Based on the preliminary research results, it was observed that 40% of patients in the moxibustion group and 10% in the placebo group exhibited a decrease of at least 3 points on the BFI at week 4. Calculations indicate that the sample size of 58 patients would ensure a study power of at least 80%, with a two-sided significance level of 0.05. To adjust for an anticipated dropout rate of 20%, 37 patients will be finally taken from for each group.

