**Methods:**

This investigation employs a randomized, controlled, single-blinded trial design. A 1:1 random allocation method will be implemented to assign 74 participants to either the moxibustion group or the placebo moxibustion group. All participants will undergo eight sessions over 4 weeks, with sessions occurring twice weekly and lasting for 30 minutes each. Assessments for follow-up will take place at week 8. The primary outcome will be the percentage of patients who show a decrease of at least three points on the Brief Fatigue Inventory (BFI) at week 4. Secondary outcomes will encompass changes in the BFI, Quality of Life Questionnaire-Core 30 (QLQ-C30), Generalized Anxiety Disorder Scale-7 (GAD-7). Meanwhile, Blood cell counts and serum T lymphocyte subsets (CD3+, CD4+, CD8+, CD4+/CD8+) will be measured as exploratory outcomes. In addition, adverse events will be screened and documented throughout the study. An analysis adhering to the intention-to-treat(ITT) principle will be executed.

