### Data analysis and statistical methods

2.10

SPSS 25.0 will be used for statistical analysis, with an ITT methodology. Missing data will be imputed with the last available evaluation. Continuous variables will be presented as mean ± standard deviation (SD) or as median with interquartile range[M (IQR)], while categorical variables will be expressed in terms of frequencies or percentages. Statistical significance will be determined at *p* < 0.05.Baseline anticancer treatment characteristics and clinically relevant concomitant treatments during the trial will be summarized descriptively; if needed, sensitivity analyses or adjusted analyses will be conducted to assess the robustness of the primary outcome.

The proportion of patients with a minimum 3-point reduction on the BFI at week 4 will be assessed using Chi-Square or Fisher’s exact tests for categorical data. For repeated measures, such as changes in BFI scores (week 1,2,3,4,8), Generalized Estimating Equations (GEE) will be employed.

GAD-7, QLQ-C30, leukocyte counts, hemoglobin levels, platelet counts, lymphocyte counts, and CD3+, CD4+, CD8+, and CD4+/CD8+ ratios are examples of continuous variables for which unpaired t-tests or Mann-Whitney U tests will be used for between-group comparisons, as applicable.

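### The 80% power claimed for 58 patients comes from a formula that matches neither planned primary test; 29 per group gives about 77–78% with chi-square and 68% if Fisher's exact test is used throughout

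*Protocol article*

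**What the plan says.** Section 2.9 takes its response rates from preliminary results: "40% of patients in the moxibustion group and 10% in the placebo group" had a BFI fall of at least 3 points at week 4. From these it states that "the sample size of 58 patients would ensure a study power of at least 80" percent, "with a two-sided significance level of 0.05". It then continues: "To adjust for an anticipated dropout rate of 20%, 37 patients will be finally taken from for each group". The abstract gives the matching total and ratio: "A 1:1 random allocation method will be implemented to assign 74 participants". Section 2.9 names neither a formula nor a test.

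Section 2.10 says that the primary responder proportion will be "assessed using Chi-Square or Fisher’s exact tests for categorical data", with no rule for choosing between the two. The same section analyses by ITT and adds: "Missing data will be imputed with the last available evaluation".

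**The concern.** A power figure belongs to a particular test, sample size and analysis set. Section 2.9 gives the size and the power, and section 2.10 gives the tests and the handling of missing data. They do not fit together in two respects.

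- **Test.** The 58 comes from an approximation that corresponds to neither named test, and both named tests have less power at that size.
- **Analysis set.** The dropout inflation treats dropouts as lost, leaving 29 evaluable patients per group. ITT with carried-forward values keeps them in the denominator, so the 58-patient calculation does not describe the planned analysis.

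At stake is a stated assurance of at least 80% on the only primary outcome of a trial whose own discussion calls the sample relatively small. At 29 per group the unstated choice of test alone moves power by about 10 points (77.8 − 68.1 = 9.7).

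**Working it through.** **Inputs.** p1 = 0.40, p2 = 0.10, two-sided alpha 0.05, power 0.80, dropout 20% (all section 2.9). Allocation is 1:1 (abstract), so 58 means 29 per group and 74 means 37 per group. The tests and the missing-data rule are from section 2.10.

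**1. The plan's own figures reproduce.** Unpooled normal approximation:

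n = (1.960 + 0.8416)² × [0.40×0.60 + 0.10×0.90] / (0.40 − 0.10)² = 7.849 × 0.33 / 0.09 = 28.8, so 29 per group and 58 in total. The power of this approximation at 29 is 80.3%.

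Dropout: 29 / (1 − 0.20) = 36.25, so 37 per group and 74 in total.

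**2. The formula that corresponds to Pearson chi-square.** With the pooled variance under the null (mean rate 0.25):

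n = [1.960 × √(2×0.25×0.75) + 0.8416 × √0.33]² / 0.09 = 31.5, so 32 per group. The same approximation gives 76.5% power at 29.

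**3. Exact power at 40% v 10%.** I enumerated all pairs of binomial counts and summed the probability of those with p < 0.05. The switching column uses Fisher when an expected count is below 5 and Pearson otherwise. That rule is an assumption, since the protocol states none.

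| Per group | Pearson, uncorrected | Switching rule | Fisher throughout |
|---|---|---|---|
| 29 | 77.8% | 77.1% | 68.1% |
| 30 | 79.6% | 79.1% | 70.5% |
| 31 | 81.3% | 80.9% | 72.7% |
| 36 | 86.4% | 86.4% | 80.0% |
| 37 | 87.5% | 87.5% | 81.5% |

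Pearson first reaches 80% at 31 per group and Fisher at 36. At 29 per group the expected number of responders is 29 × (0.40 + 0.10) / 2 = 7.25 per arm. Under the assumed rule Fisher would therefore replace Pearson in only about 4.9% of trials.

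**4. The planned ITT analysis, 37 per group.** Power now depends on how often a dropout's carried-forward value counts as a response. The protocol does not give this, so the rows are assumptions.

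| Assumption about the 20% who drop out | ITT rates | Pearson | Switching rule | Fisher |
|---|---|---|---|---|
| Same response rate as completers | 40% v 10% | 87.5% | 87.5% | 81.5% |
| Half the completer rate | 36% v 9% | 82.5% | 82.3% | 75.1% |
| 30% of the completer rate | 34.4% v 8.6% | 80.3% | 79.9% | 72.2% |
| None respond (worst case) | 32% v 8% | 76.6% | 75.8% | 67.5% |

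The rates are the completer rate × (0.80 + 0.20 × relative rate); for example, 40% × (0.80 + 0.20 × 0.5) = 36%.

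**The case against.** The strongest defence has four parts.

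- **The 58 is a legitimate calculation.** It follows from a standard textbook formula, and the dropout step is done correctly. This stands. The fault is a mismatch between formula and test, and against Pearson it amounts to about 2 points of exact power, or 2 patients per group (31 against 29).
- **Fisher throughout is not clearly the plan.** A reader might infer that about one true effect in three would be missed. That follows only if Fisher is always used. Under the usual expected-count rule it would hardly ever be used, and power stays at 77.1%. This largely stands, although section 2.10 states no rule and so does not exclude Fisher.
- **The primary analysis has 74 patients, not 58.** If 40% and 10% hold in the ITT set, both tests exceed 80%. This stands under that condition.
- **The worst case is not what the protocol implies.** A reader might infer that going to 37 per group cannot repair the shortfall because dropouts become non-responders. The documents do not support that. BFI is scheduled weekly during treatment (Table 1 and section 2.7.3.1), so a patient who leaves after week 2 or 3 can carry forward a response. Section 2.9 does not say that all dropout falls before week 4, and a patient lost between weeks 4 and 8 already has the primary outcome. So 32% v 8% is a lower bound, not a forecast.

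What the defence does not rescue is the sentence itself. It promises at least 80% for 58 patients, and no test named in section 2.10 gives that. Leaving the formula's name to a fuller document would be ordinary condensation, but the stated figure would still not match the stated tests.

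**Conclusion.** The power statement in section 2.9 is wrong as written for the planned tests. The gap at 29 evaluable per group is 2 to 3 points with chi-square (77.1% to 77.8% by enumeration, 76.5% by the pooled formula) and about 12 points if Fisher is used throughout. The 29-per-group figures rest only on the protocol's own inputs, apart from the assumed switching rule.

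For the 74 patients actually planned, chi-square power lies between about 77% and 87%, and Fisher between about 68% and 82%. The position within each range depends on the response rate among dropouts, which is an assumption. Chi-square still reaches about 80% when dropouts respond at only 30% of the completer rate. The documents therefore do not support calling the trial clearly underpowered, or its size miscalculated. Severity is moderate: the claim and the test rule need correcting, but the number of patients need not change.

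**What to change.** Keep 74 patients.

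- **Section 2.9:** name the unpooled formula as the source of 58. State power as about 77–78% with chi-square for 29 evaluable per group. For 37 per group under ITT with carried-forward values, give the range of about 77% to 87% with chi-square. State that the upper end assumes 40% v 10% in all randomised patients, and the lower end assumes that all of the 20% who drop out are non-responders.
- **Section 2.10:** name uncorrected Pearson chi-square as the primary test, or state the rule for switching to Fisher's exact test. Either is acceptable, provided that the power quoted in 2.9 is for the test that will be used.

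The cost is a few reworded lines and a slightly less favourable power statement. No extra patients are needed.
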